### Data analysis

The primary outcomes for this pilot trial require descriptive statistics for recruitment, completion of primary assessment, retention, and adverse effect profiles. For exploratory outcomes, change in NPRS, HIT-6, and QOLIBRI at 1 and 3 months following intervention for patients receiving PRP compared to steroid/anesthetic and normal saline will be analyzed. A two-way mixed ANOVA test will be completed to evaluate the change in NRPS between groups. Chi-square testing will be performed to determine the relationship between basic characteristics in the three groups. For secondary outcomes, Kruskal-Wallis non-parametric analysis based on ranks will be completed correcting for multiple comparisons with Bonferroni correction. All results will be presented with 95% confidence intervals. Results will be preliminary and should be interpreted with caution due to the small sample size.

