**Methods:**

Thirty adults (over 18 years of age) with post-traumatic GON will be randomized into one of three groups: (1) autologous PRP injection, (2) steroid/anesthetic injection (standard care), or (3) placebo injection with normal saline. Injections will be performed to the greater occipital nerve under ultrasound guidance by a trained physician. Daily headache intensity and frequency data will be collected pre-injection and for the duration of the study period. Feasibility will be defined as greater than 30% recruitment, 70% completion of intervention, 70% retention, and less than 2 minor adverse events. Exploratory outcomes will be explored using the Headache Impact Test-6 (HIT-6, a valid and reliable 6-item questionnaire for assessment of the impact of headaches across different diagnostic groups of headaches) and the quality of life in following brain injury questionnaire (QOILIBRI).

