### Blinding and randomization

Each participant will be randomized following screening and enrollment in the study. Participants will be randomized (via sealed envelope) by a blinded research assistant in a 1:1 fashion to one of three treatment arms: (1) autologous PRP injection, (2) steroid/anesthetic injection (standard care), or (3) placebo injection with normal saline. All patients will undergo 60 mL blood draw on their scheduled day of injection. Whole blood samples will be prepared in the PRP group only; otherwise, they will be discarded appropriately. Syringes (3 mL each) will be prepared by a research assistant and will be covered in an opaque tape so the physician providing the injection is blinded to the type of injectate. The physician will fill out a questionnaire at the time of injection indicating their best guess of the syringe contents, which will be evaluated afterwards, to ensure adequate blinding. Unblinding will occur only in extraordinary circumstances if knowledge of the actual treatment received is deemed essential to providing further patient care.

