### Exploratory outcomes

The primary exploratory outcome will be a reduction in the numeric pain rating scale (NPRS) at 3 months in the PRP group, as compared to the steroid and placebo groups. The suggested minimal clinical important difference (MCID) at the time of writing is 2 points [41] or ≥ 50% compared to placebo. Secondary outcomes will include headache frequency based on daily diaries and NPRS. Additional questionnaires completed at 2 weeks prior to injection, 1 week, 1 month, and 3 months post-injection will be the Headache Impact Test-6 (HIT-6; a valid and reliable 6-item questionnaire for assessment of the impact of headaches across different diagnostic groups of headaches [42, 43]) and the quality of life in following brain injury questionnaire (QOILIBRI). As well, participants will complete daily medication diaries tracking prn analgesic use.

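### The two-way mixed ANOVA named for NPRS does not estimate the two 3-month PRP-versus-comparator differences that the protocol sets as its main exploratory outcome

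*Protocol article*

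**What the plan says.** The Exploratory outcomes section defines the main exploratory outcome as "a reduction in the numeric pain rating scale (NPRS) at 3 months in the PRP group, as compared to the steroid and placebo groups", and gives 2 points (or at least 50% compared with placebo) as the minimal clinically important difference.

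The Data analysis section says that change in NPRS, HIT-6 and QOLIBRI at 1 and 3 months will be analysed for PRP against each comparator. For NPRS it then names the method: "A two-way mixed ANOVA test will be completed to evaluate the change in NRPS between groups". For the rest: "For secondary outcomes, Kruskal-Wallis non-parametric analysis based on ranks will be completed correcting for multiple comparisons with Bonferroni correction". It adds: "All results will be presented with 95% confidence intervals". The same section calls the results preliminary because of the small sample.

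Three other places bear on the choice:

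- Measures: questionnaires and the daily diary start 2 weeks before injection, so a baseline is available. Questionnaires follow at 1 week, 1 month and 3 months.
- Primary outcomes: feasibility is met with 70% of recruits attending the injection and 70% of those injected completing 3 months.
- Attrition and adherence: participants who change routine medication or do not complete questionnaires are withdrawn.

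**The concern.** The outcome is two numbers: the PRP-minus-steroid and PRP-minus-saline differences in NPRS reduction at 3 months. The named method gives F tests of whether the three groups differ somewhere, in level or in course over time. Such a test can be significant because steroid differs from saline, or because of something that happened at 1 month.

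This matters more here than in many trials. The Background puts the mean relief from a nerve block at about 1 month, so an early steroid effect is expected and any PRP advantage over steroid should show at 3 months. A reader could take a significant ANOVA as support for PRP when its 3-month result is no better than steroid's.

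The pilot is also meant to inform a larger trial. The quantities useful for that are the 3-month differences with intervals and a residual SD, and the named tests do not report these directly. Two secondary points follow from the same choice: precision is lost when baseline is not a covariate, and records may be lost when a visit is missing.

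**Working it through.** The documents give no SD, correlation or power figure, so there is no stated figure to reproduce. SD and correlation (rho) below are assumptions.

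**1. Sample.** "Thirty adults (over 18 years of age) with post-traumatic GON will be randomized into one of three groups", allocated "in a 1:1 fashion to one of three treatment arms": 30 / 3 = 10 per arm.

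**2. What the omnibus test responds to.** Simulation with 4,000 runs per scenario, 10 per arm, SD 2, rho 0.5 and mean baseline 6. The group-by-time F test (baseline, 1 month, 3 months) is set against baseline-adjusted 3-month contrasts, all at the 5% level.

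| True pattern | Interaction F rejects | PRP vs steroid, 3 months | PRP vs saline, 3 months |
|---|---|---|---|
| No effect | 5.0% | 5.2% | 5.2% |
| Steroid better by 3 points at 1 month only | 94.7% | 5.6% | 5.0% |
| PRP = steroid, both 2 points better than saline at 1 and 3 months | 61% | 4.9% | 69% |
| PRP better by 2 points at 3 months only | 61% | 68% | 68% |

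The F test keeps its error rate, so it is valid. It answers a different question: rows 2 and 3 show it rejecting often when PRP has no 3-month advantage over steroid.

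**3. Baseline.** With equal variances, the variance of a 3-month arm difference is proportional to 2(1 - rho) for change scores and to 1 - rho² with baseline as a covariate. The ratio is (1 - rho²) / [2(1 - rho)] = (1 + rho) / 2:

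- rho 0.3: 1.3 / 2 = 0.65
- rho 0.5: 1.5 / 2 = 0.75
- rho 0.7: 1.7 / 2 = 0.85

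In NPRS points, at SD 2 and rho 0.5, the 95% half-width is t × SD × √(2/n) × √(variance factor):

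- 10 per arm, change score: 2.052 × 2 × √0.2 × √1 = 1.84
- 10 per arm, baseline-adjusted: 2.056 × 2 × √0.2 × √0.75 = 1.59
- 5 per arm, change score: 2.179 × 2 × √0.4 × √1 = 2.76
- 5 per arm, baseline-adjusted: 2.201 × 2 × √0.4 × √0.75 = 2.41

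**4. Incomplete records.** At the protocol's own thresholds, 30 × 0.70 = 21 are injected and 21 × 0.70 = 14.7 complete 3 months, or about 5 per arm. A classical mixed ANOVA would use only those with every time point. The thresholds are floors for feasibility, not forecasts.

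**5. Intervals beside Kruskal-Wallis.** The test returns a p-value. Exact pairwise Hodges-Lehmann intervals are available at these sizes, with actual coverage of 95.7% (10 per arm), 96.2% (7) and 96.8% (5). The promised intervals can therefore be produced, but no estimator is named for them.

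**The case against.** The strongest reply is that these are exploratory outcomes of a feasibility pilot, that the article condenses a fuller plan, and that follow-up contrasts and missing-data rules are usual analysis-plan content. The Data analysis section does say that PRP will be compared with each comparator at 1 and 3 months. This limits the weight of the point. It does not remove it, because the article does name a method for NPRS, and that method does not yield the outcome it defines.

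Several stronger readings are tempting and are not supported:

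- **Baseline is ignored.** It is not. Change is analysed, so baseline enters by subtraction or as a time level. Change score and covariate adjustment are both unbiased under randomisation; the difference is precision.
- **Incomplete participants will be dropped.** No listwise rule is written. Complete-case use is a property of classical mixed ANOVA. If dropout is monotone, it removes mainly people already missing at 3 months.
- **Kruskal-Wallis rules out intervals.** It does not. The Bonferroni wording suggests pairwise follow-up, and rank-based intervals exist.
- **The ANOVA halves the effect.** If PRP gains 2 points at both times and steroid only at 1 month, the PRP-steroid difference averaged over time is (0 + 2) / 2 = 1.0 instead of 2.0. That holds only for the group main effect on change scores. In that pattern, with saline flat and the same assumptions, the interaction test rejects in 81% of runs and the main effect in 59%. The interaction is not diluted, though it is still omnibus.
- **The baseline chi-square tests are invalid.** The text is "Chi-square testing will be performed to determine the relationship between basic characteristics in the three groups". It does not say that age or weight will be tested this way. For a binary characteristic with 10 per arm, exact enumeration gives a true size of 3.7% to 5.0% for prevalences from 0.1 to 0.45, so there is no inflation. At most, a descriptive table would serve better.

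**Conclusion.** The point holds in limited form. The protocol defines its main exploratory outcome as two 3-month differences and names for it a valid omnibus analysis that does not estimate them. Under the assumed SD of 2 and correlation of 0.5, that analysis can reject in 61% to 95% of runs when PRP has no 3-month advantage over steroid.

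The precision gain from adjusting for baseline is real but depends on a correlation that the document does not give: a 15% to 35% reduction in variance for rho between 0.7 and 0.3. The loss of incomplete records is a likely consequence of the method together with the attrition that the protocol allows, not a stated rule. The interval gap is an unnamed estimator, not an impossibility.

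A reader might infer that the trial's conclusions are at risk. They are not: the primary outcomes are descriptive feasibility measures and do not depend on any of these tests. What is at stake is how the exploratory pain result is read and how well the pilot informs the next trial.

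**What to change.** In Data analysis, replace the two-way mixed ANOVA with a linear mixed model of post-injection NPRS, with arm, time, arm-by-time and baseline NPRS as fixed effects, and keep participants with partial follow-up. Report the two 3-month contrasts, PRP versus steroid/anesthetic and PRP versus saline, each with a 95% confidence interval, and the residual SD for planning the larger trial.

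For HIT-6, QOLIBRI and headache frequency, either use the same baseline-adjusted model or keep the rank test and name the interval that goes with it, for example Hodges-Lehmann.

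The cost is a change of wording and slightly more analysis work. No extra data are needed, and the article says that recruitment was still under way at submission. The limits should be stated: the model is fitted to about 10 or fewer participants per arm, and it recovers nothing on outcome for people with no post-injection values. At the attendance threshold that could be 30 - 21 = 9 of the 30.

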### Study status

At the time of submission, we are recruiting and enrolling participants in the study.

### Protocol amendments

Any modifications to the study protocol will be submitted and approved through the University of Calgary Conjoint Health Research Ethics Board. The ClinicalTrials.gov registry will be updated as required, and trial participants will be notified of relevant study modifications.

### Access to data

The principal investigator, research assistants, students, and statistician colleagues who are directly involved in the study will have access to the final data set.

### Dissemination policy

Trial results will be disseminated through presentations at conferences, invited presentations, and published manuscripts by study authors and contributors. The study is registered on clinicaltrials.gov. There will be no use of professional writers.

## Discussion

GON in the post-traumatic setting is a debilitating condition without effective long-term treatment options. GON can be seen commonly following concussion, especially in cases of posterior head trauma or associated whiplash injury. PRP has been studied extensively across multiple degenerative conditions but has only recently been evaluated as a potential treatment for peripheral neuralgias. PRP has the proposed advantage of restoring normal nerve physiology and spares the use of steroids, which are associated with multiple adverse effects, especially when provided repeatedly over the long term. In addition to improved management of chronic pain, patients may experience enhanced function, quality of life, and reduced medication usage. This pilot study will provide evidence to explore whether a larger double-blinded randomized controlled trial for the treatment of GON in patients with post-traumatic headache with PRP is feasible. Feasibility will be based on successful recruitment, completion of the primary intervention, retention, and adverse events.

## Data Availability

Not applicable.

## Abbreviations

GON: Greater occipital neuralgia
HIT-6: Headache impact test
ICHD: International classification of headache disorders
MCID: Minimal clinical important difference
NPRS: Numerical pain rating scale
PRP: Platelet-rich plasma
PTH: Post-traumatic headache
QOILIBRI: Quality of life in following brain injury questionnaire
TBI: Traumatic brain injury
US: Ultrasound
